## Abstract

Recurrent implantation failure (RIF) is a common issue in frozen-thawed embryo transfer (FET). Prior to transfer, uterine endometrial receptivity of FET patients can be assessed using multimodal transvaginal ultrasound indicators to predict the success rate of the current FET cycle. Endometrial blood flow is a crucial element in evaluating endometrial receptivity. MV-FLOW^™^ is an advanced two-dimensional superb microvascular imaging technology that can detect and display blood flow in micro-vessels. The data for this study were obtained from an ongoing cross-sectional study comprising 323 RIF patients and 323 first implantation (FI) patients, who underwent transvaginal ultrasound before FET. We collected basic clinical data and multimodal ultrasound data from these patients as predictive features, with clinical pregnancy as the predictive label, for model training. Based on the above, this study aims to establish and validate a clinical prediction model for FET outcomes using support vector classification (SVC) algorithms, based on MV-FLOW^™^ and multidimensional transvaginal ultrasound imaging features. The objective is to determine the predictive role of multimodal transvaginal ultrasound in embryo transfer outcomes and provide evidence for the clinical application of MV-FLOW^™^.

**Trial registration:**
*Trial Registration*: ChiCTR2400086401.

## Introduction

Recurrent implantation failure (RIF) marks a pivotal point in multiple embryo transfers (ETs), potentially impacting future success and requiring specialized diagnostics and treatments for live birth attainment [1]. Until recently, the definition of RIF has been multifaceted, contingent upon variables including female age, the nature of the transferred embryos, and whether the transfers were conducted with fresh or frozen embryos [2]. The heterogeneity of the biological basis for these definitions has led to challenges [3], affecting patients and reproductive medicine professionals, resulting in unreliable and contradictory outcomes and conclusions [1]. An initial study has revealed that, in the absence of discernible extrinsic factors, aneuploid blastocysts exhibit comparable rates of ongoing implantation and live birth following the first three consecutive single embryo ET. Among 4,429 women, this cohort demonstrated a cumulative implantation probability of 95.2% and a cumulative live birth probability of 92.6% [4]. These findings corroborate mathematical models derived from literature-reported implantation and live birth rates of aneuploid blastocysts [1]. Consequently, these studies suggest that the prevalence of "true" unexplained RIF within the IVF population is less than 5%, given that no statistically significant progressive decline in implantation or live birth rates was detected across the first three consecutive groups of aneuploid blastocyst transfers.

Nonetheless, certain scholars harbor reservations about this viewpoint [5] given that the study’s subjects all underwent costly preimplantation genetic testing for aneuploidies (PGT-A) and endometrial receptivity analysis (ERA) diagnostics, limiting their applicability across all in vitro fertilization (IVF) patients. In 2023, the European Society of Human Reproduction and Embryology (ESHRE) [6] recommended a 60% threshold for cumulative predicted implantation opportunity in recurrent implantation failure (RIF) to differentiate between euploid and aneuploid embryo transfers. Pre-transfer multimodal vaginal ultrasound indicators are routinely used in clinical practice to assess endometrial receptivity in FET patients, serving as a diagnostic tool to predict FET success rates. Endometrial blood flow, primarily assessed via 2D ultrasound following the Applebaum criteria [7], is crucial for evaluating blood flow velocity and direction through the Doppler effect. Endometrial blood flow is a crucial aspect of endometrial receptivity assessment, primarily through 2D ultrasound mode, following the Applebaum criteria for detecting and classifying endometrial blood flow signals. Its principle involves utilizing the Doppler effect of ultrasound waves to evaluate blood flow velocity and direction. Specifically, when the ultrasound beam encounters moving red blood cells, it generates a frequency change proportional to the blood flow velocity. By analyzing this frequency change, the blood flow velocity can be calculated, thereby assessing the richness of blood flow and vascular resistance. MV-FLOW^™^ is an advanced spatiotemporal coherent superb microvascular imaging technology capable of detecting and displaying blood flow in small vessels. Studies have shown [8–10] that MV-FLOW^™^ can display low-speed blood flow in normal or diseased tissues (such as tumors), with high sensitivity and resolution. Our previous research [11] observed the effects of acupuncture on MV-FLOW^™^ in RIF patients on the day before implantation, suggesting that MV-FLOW^™^ is a sensitive indicator of endometrial blood flow and that acupuncture can exert immediate regulatory effects on this indicator. However, the predictive value and advantages of MV-FLOW^™^ for embryo transfer remain unclear.

This study, grounded in a current cross-sectional investigation employing support vector classification (SVC) algorithms, aims to explore: (1) the predictive precision of MV-FLOW^™^ endometrial vascular distribution indices and/or endometrial vascular indices for FET outcomes in RIF patients; (2) the potential of these indices to categorize patients as either successful first implantation (FI) or RIF.

## Methods and materials

### Study design

We will recruit a cross-sectional observational cohort of FI and RIF patients from Jinxin Sinan Women’s and Children’s Hospital in Sichuan who underwent FET. These patients will undergo transvaginal ultrasound examination, including assessment of endometrial MV-FLOW^™^ prior to embryo transfer in FET. First, the foundational clinical data of RIF patients, along with endometrial ultrasound-related indices, will serve as features to forecast the clinical outcome of FET. Subsequently, a clinical prediction model grounded in multidimensional ultrasound features will be developed. The efficacy of this model will be rigorously assessed and subjected to cross validation. Then, the characteristics observed under transvaginal ultrasound examination in successful FI and RIF patients will be employed as predictive indicators to ascertain whether they can effectively categorize successful FI and RIF patients post-transplantation. The dates of the recruitment are July 15^th^, 2024 to July 15^th^, 2025. We will also establish a flexible recruitment timeline, allowing for adjustments as needed, and regularly monitor and evaluate the recruitment progress, enabling us to identify and address any issues promptly. All obtained private data will be subject to the supervision of the ethics committee, and the study will be conducted after patients have signed the informed consent form. This trial was reviewed by the ethics committee of Sichuan Jinxin Xi’nan Women’s and Children’s Hospital (2023–006), and registered in Chinese Clinical Trial Registry (ChiCTR2400086401) (See S1 Table). Study flow chart see Figs 1 and 2 and S2 Table (the SPIRIT schedule of enrollment).

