### Participants and sample size

#### Diagnostic criteria for RIF patients

According to the definition of RIF proposed by EHSRE 2023 [12], the transfer of embryos considered viable fails to result in a positive pregnancy test for a given patient and is insufficient to consider further investigation and/or intervention. Considering that the recommended threshold for the cumulative predicted chance of implantation for RIF is 60%, when a couple does not successfully implant by transferring a certain number of embryos and the cumulative predicted chance of implantation associated with that number is greater than 60%, then they should be advised to undergo further investigations and/or treatment options.

For embryos of unknown euploidy [13], RIF is diagnosed in female patients under 35 years old after three or more embryo transfers (ET); for those aged 35 to 39, after four or more ETs; and for those aged 40 and above, after six or more ETs. For embryos with known ploidy status [14], RIF is diagnosed after two or more ETs.

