#### Sample size calculation

This study is a cross-sectional trial to establish a predictive model for endometrial receptivity and pregnancy outcomes using SVC to predict clinical pregnancy. The ultrasound assessments of uterine arteries and endometrial thickness are crucial for pre-implantation evaluation of endometrial receptivity, a study involving 78 FET patients (resulting in 45 clinical pregnancies, 57.7%) utilized elastic ultrasound imaging and nine predictive indicators based on basic information, achieving a predictive accuracy of 76.92% [15]. Sample size estimation was conducted using “pmsampsize” in R software [16]. According to the definition of RIF, at least two failed ETs were diagnosed as RIF. Assuming a clinical pregnancy rate of 30%, a minimum of 323 RIF patients were required for sample estimation. In a 1:1 ratio, 323 FI patients were also included. The code for sample size calculation is referenced in S1 Fig.

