### Clinical data acquisition

We will systematically compily comprehensive clinical data for RIF or FI patients, encompassing their foundational details such as chief complaints, present illness history, past medical history, family history, allergy history, pertinent examination findings, comorbid conditions, and medication use. Additionally, we will meticulously document their prior clinical information from assisted reproductive technology (ART) treatments, including treatment protocols, cycle specifics, and outcomes.

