However, most prior studies have relied on retrospective analysis, potentially yielding biased results. Hence, prospective research remains essential to evaluate the feasibility and precision of ultrasound-derived uterine blood flow parameters in predicting the optimal embryo transfer timing in IVF. This protocol outlines a prospective, cross-sectional study that explores the role of ultrasound in pre-embryo transfer diagnostics. Building on this, we have pioneered the use of MV-FLOW^™^ to detect microvascular distribution within the endometrium and sub-endometrium, and validated its feasibility in assessing endometrial vasculature [11]. SVC [25] is a common supervised machine learning algorithm that seeks an optimal hyperplane in feature space to discriminate between different classes, characterized by excellent generalization capabilities. We propose to input all ultrasound-derived uterine blood flow parameters as flow features to predict embryo implantation outcomes and rates, thereby identifying the most predictive ultrasound indices for embryo implantation and discussing the diagnostic value of MV-FLOW^™^ in assessing endometrial receptivity. RIF is predominantly influenced by embryonic or uterine factors, with studies indicating abnormal blood flow parameters [26]. Our study extends this by investigating the clinical utility of these parameters in differentiating between successful first-time transfers and RIF cases, offering predictive markers for RIF identification.

In conclusion, while we have discussed the potential effects of MV-FLOW^™^ in predicting frozen embryo transfer outcomes in patients with recurrent implantation failure, it is important to consider the broader clinical implications should our study’s predictions prove accurate. Successful prediction models could revolutionize personalized treatment plans, allowing clinicians to tailor interventions more effectively and improve overall success rates in assisted reproductive technologies. This could lead to a paradigm shift in how recurrent implantation failure is managed, ultimately enhancing patient outcomes and satisfaction. Furthermore, the integration of MV-FLOW^™^ with multidimensional ultrasound features could pave the way for more comprehensive diagnostic tools, offering deeper insights into the underlying causes of implantation failure and facilitating more targeted therapeutic strategies.

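### The pregnancy model as described names no feature of the transferred embryo, so it cannot show whether MV-FLOW predicts beyond known embryo determinants

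*Protocol article*

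**What the plan says.** All references are to the protocol article.

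- **Inputs.** Under Study design, "the foundational clinical data of RIF patients, along with endometrial ultrasound-related indices, will serve as features to forecast the clinical outcome of FET". The Abstract agrees: "We collected basic clinical data and multimodal ultrasound data from these patients as predictive features, with clinical pregnancy as the predictive label". The Discussion narrows to ultrasound: "We propose to input all ultrasound-derived uterine blood flow parameters as flow features to predict embryo implantation outcomes and rates".
- **Data collected.** Clinical data acquisition lists complaints, histories, examination findings, comorbidity and medication, and then "prior clinical information from assisted reproductive technology (ART) treatments, including treatment protocols, cycle specifics, and outcomes". That last item concerns earlier treatments, not the study transfer.
- **Eligibility.** The inclusion and exclusion criteria cover age, FI or RIF status, endometrial preparation, consent and maternal conditions. They set no limit on the number, stage, grade or ploidy of the embryo transferred.
- **Ploidy.** It appears in the RIF definition only: "For embryos with known ploidy status [14], RIF is diagnosed after two or more ETs", against three, four or six transfers by age band for embryos of unknown ploidy. Both kinds of patient are eligible.
- **Evaluation.** The Clinical prediction model section ranks features by SVC weight and permutation importance and reports accuracy, F1 and AUC. It describes no comparison of models with and without MV-FLOW.
- **Interpretation.** The Sample size calculation section states the purpose as to "establish a predictive model for endometrial receptivity and pregnancy outcomes using SVC to predict clinical pregnancy". The Discussion intends to draw conclusions on the diagnostic value of MV-FLOW for receptivity, and itself says that "RIF is predominantly influenced by embryonic or uterine factors".

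**The concern.** Clinical pregnancy after one transfer is a joint result of embryo and endometrium. A patient with a receptive endometrium and a poor embryo is labelled a failure, and the reverse also happens. For pure prediction from chosen inputs this is tolerable. It becomes a problem when the model is read as a measure of receptivity and the ranking as evidence for MV-FLOW.

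Two things are at stake. First, the clinic already knows what it is transferring, so the useful question is whether MV-FLOW adds to that knowledge, and a ranking among patient and ultrasound features does not answer it. Second, if MV-FLOW indices are associated with embryo type or number, for instance through endometrial regimen or patient selection, an unmeasured embryo effect can appear as an MV-FLOW effect.

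**Working it through.** **1. The plan's own figure.** The stated minimum is 323 RIF patients at a 30% pregnancy rate. The outcome-proportion criterion of pmsampsize gives (1.96/0.05)² × 0.30 × 0.70 = 322.69, rounded up to 323. This reproduces exactly, but the criterion contains no term for predictors. The figure therefore says nothing about which features the model needs, or how many it can carry.

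**2. How much can ploidy status carry?** Inputs: the 60% cumulative threshold and the transfer counts in the RIF definition. Assume the threshold is first passed at count n. The chance per transfer then lies between 1 − 0.4^(1/n) and 1 − 0.4^(1/(n−1)).

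| Category | n | Lower | Upper | Midpoint |
|---|---|---|---|---|
| Known ploidy | 2 | 36.8% | 60.0% | 48.4% |
| Unknown, under 35 | 3 | 26.3% | 36.8% | 31.5% |
| Unknown, 35 to 39 | 4 | 20.5% | 26.3% | 23.4% |
| Unknown, 40 and over | 6 | 14.2% | 16.7% | 15.5% |

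For a two-level predictor, AUC = 0.5 + (s − f)/2, where s and f are the shares of tested patients among pregnant and non-pregnant women. Assume the three age bands are equally common among untested patients, so that their mean chance is 20.3% (lower bounds) or 23.5% (midpoints). The fraction tested is not in the documents, so it is varied.

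| Assumed fraction tested | AUC, lower bounds | AUC, midpoints |
|---|---|---|
| 25% | 0.58 | 0.61 |
| 10% | 0.54 | 0.56 |
| 5% | 0.52 | 0.53 |

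Example, 25% at lower bounds: the overall rate is 0.25 × 0.368 + 0.75 × 0.203 = 0.244. Then s = 0.0919/0.244 = 0.376 and f = 0.25 × 0.632/0.756 = 0.209, so AUC = 0.5 + 0.167/2 = 0.58.

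**3. Embryo number (illustration).** With an assumed 20% chance per embryo, two embryos give 1 − 0.8² = 36%. An assumed even split of one and two embryos gives an AUC of about 0.60.

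**4. What omission does to the MV-FLOW gain.** This is a large-sample logistic simulation with 300,000 records per scenario and a 30% event rate. Assumed log-odds per SD are 0.7 to 1.0 for the embryo factor and 0.3 for another clinical factor. None of these effects or correlations comes from the documents.

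| True MV-FLOW log-odds | Embryo/MV-FLOW correlation | AUC gain, embryo omitted | AUC gain, embryo included |
|---|---|---|---|
| 0 | 0 | 0.000 | 0.000 |
| 0 | 0.2 | 0.007 to 0.014 | 0.000 |
| 0 | 0.4 | 0.027 to 0.047 | 0.000 |
| 0.4 | 0 | 0.048 to 0.049 | 0.018 to 0.025 |
| 0.4 | 0.2 | 0.079 to 0.085 | 0.016 to 0.022 |
| 0.4 | 0.4 | 0.108 to 0.124 | 0.013 to 0.018 |

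False credit needs correlation. In the zero-correlation row with a true effect, the two gains differ only because the first is measured over a weaker base model. That is not confounding, but it is still a different answer to the question of what MV-FLOW adds.

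**5. Room for more parameters.** By the shrinkage criterion (target 0.9), 323 patients support about 3, 6, 9 and 13 parameters at an anticipated AUC of 0.70, 0.75, 0.80 and 0.85. The documents state neither the number of parameters nor the anticipated performance.

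**The case against.** **Silence is not exclusion.** No closed feature list is given. The clinical data are described in open terms, and this is a condensed article whose figures and supplementary tables are not shown. This stands in part: the embryo variables are unnamed, not ruled out. But every description of the inputs omits them, the only neighbouring sentence is confined to earlier treatments ("we will meticulously document their prior clinical information from assisted reproductive technology (ART) treatments"), and the ultrasound variables are listed down to single Doppler parameters.

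**A prediction model is valid on its chosen inputs.** The Introduction asks for predictive precision, and a reader might infer from this point that the endpoint is unusable or that nothing can be learned about MV-FLOW. The documents do not support that. Prediction from the stated inputs is legitimate, and added value over the other ultrasound indices can be estimated. The limit concerns added value beyond embryo determinants and the receptivity reading.

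**The protocol's thresholds mostly reflect age.** A reader might take the spread across all four RIF categories as the embryo effect: with an equal mix they give an AUC of 0.62 (lower bounds) to 0.66 (midpoints). That would be wrong. The three age bands alone give 0.58 to 0.60, and age is very probably among the basic clinical features. This objection stands in full, which is why only the ploidy-only range is used here.

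**False credit is not shown.** It requires a correlation between MV-FLOW and embryo characteristics, and the documents give none. Any route through age closes if age is a feature. This stands: the harm is possible, not demonstrated.

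**More predictors strain 323 patients.** Going from an assumed 9 to 13 parameters raises the required number from 734 to 1060 at AUC 0.70, from 463 to 668 at 0.75, and from 323 to 448 at 0.80; at 0.85 it stays at 323. This stands as a reason to keep the embryo set small, not to leave it out.

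**Conclusion.** The concern holds in a limited form. As described, the model names no characteristic of the embryo in the study transfer, the design does not hold those characteristics constant, and MV-FLOW is assessed by ranking only. The analysis therefore cannot show whether MV-FLOW predicts pregnancy beyond what is known about the embryo, although the protocol intends a conclusion about receptivity and diagnostic value and itself names embryonic factors.

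The size is uncertain. Ploidy status alone is worth an AUC of about 0.52 to 0.61 if 5% to 25% of patients have tested embryos, assuming that the 60% threshold is first crossed at the stated counts and that age bands are equally mixed. Number, stage and grade would come on top, with no usable figures in the documents. In the simulation, a worthless MV-FLOW index gained 0.007 to 0.047 in AUC at assumed correlations of 0.2 to 0.4, and nothing at zero correlation. Direction and size for this trial therefore depend on an association that the documents do not report. This is a worthwhile, inexpensive improvement, not a fatal flaw.

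**What to change.** 1. **Clinical data acquisition:** add, for the index transfer, the number of embryos, cleavage or blastocyst stage, morphological grade, and PGT-A status or result, abstracted from existing laboratory records. If the full protocol already collects them, say so.
2. **Clinical prediction model:** prespecify a small base set of age plus these embryo variables. Exempt it from the correlation and variance filters. Read literally, a variance threshold of 0.8 would remove any 0/1 variable, whose variance p(1 − p) is at most 0.25, so stage or PGT-A status coded that way would be lost.
3. **Evaluation:** report the performance of the base model and of the base model plus ultrasound and MV-FLOW in the same validation scheme, and rest the MV-FLOW conclusion on the difference. Keep the feature ranking as descriptive.
4. **Sample size calculation:** state the number of candidate parameters and the anticipated performance, so that 323 can be checked against more than the outcome-proportion criterion.

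**Cost:** a few fields per patient and some protocol wording, with no added procedures. The extra parameters press on a sample that may already be tight, so the base set should stay compact; if the shrinkage criterion is adopted, the required number may rise as shown under the objection. The apparent gain from MV-FLOW may also turn out smaller.

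### Objective 2 selects first-implantation patients on a later pregnancy but not RIF patients, so its AUC cannot be read as identifying RIF

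*Protocol article*

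**What the plan says.** The second aim in the Introduction is "to categorize patients as either successful first implantation (FI) or RIF". The Study design section repeats it: ultrasound characteristics "in successful FI and RIF patients will be employed as predictive indicators to ascertain whether they can effectively categorize successful FI and RIF patients". The Discussion describes the same step as "differentiating between successful first-time transfers and RIF cases" and presents the result as a source of markers for recognising RIF.

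The diagnostic criteria define FI by transfer history alone (no earlier fresh or frozen transfer), so *successful* adds a condition on the outcome of the current cycle. The note to Fig 2 places the ultrasound on the day before transfer and clinical pregnancy at 28 days after it. No section puts an outcome condition on RIF patients. The Sample size calculation assumes that 30% of them conceive and adds: "In a 1:1 ratio, 323 FI patients were also included".

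On objective 1, the Introduction, Study design and Sample size calculation tie the pregnancy model to RIF patients. The Abstract introduces both groups and then describes data "from these patients as predictive features, with clinical pregnancy as the predictive label, for model training".

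**The concern.** The stated contrast differs in two ways at once: transfer history (FI or RIF) and this cycle's outcome (all pregnant on one side, a mixture on the other). FI patients whose transfer fails are left out, although FI status does not depend on outcome.

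Objective 1 supposes that the ultrasound indices predict pregnancy. If they do, the successful FI patients are a favourable subset on those same indices and will differ from an unselected RIF group whether or not RIF patients as a whole differ from FI patients as a whole. The study could then report a marker of RIF that is only a marker of the current cycle's success.

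**Working it through.** **The plan's own figure.** Estimating a 30% risk to within ±0.05, one of the pmsampsize criteria for a binary outcome, needs (1.96/0.05)² × 0.30 × 0.70 = 322.69, rounded up to 323. This matches the stated number. The figure concerns the pregnancy rate in RIF patients; no separate size is stated for objective 2.

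**Inputs.**
- 323 RIF and 323 FI patients: Sample size calculation.
- q, the FI pregnancy rate: not given. The only other rate in the article is 57.7% (45 of 78) in a cited cohort of frozen-transfer patients. I take 30% to 60%.
- A, the marker's AUC for pregnancy among FI patients: not given. I take 0.60 to 0.75.

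**Null.** The marker has one distribution, the same in all FI and all RIF patients, so there is no group difference to find.

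**Formula.** Under this null, a randomly chosen RIF patient has the marker distribution of the whole FI group: a share q distributed like FI successes and a share 1 − q like FI failures. A successful FI patient outranks the first kind with probability 0.5 and the second with probability A. Hence AUC(successful FI vs all RIF) = 0.5q + (1 − q)A.

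At q = 57.7%:
- A = 0.65: 0.5 × 0.577 + 0.423 × 0.65 = 0.563
- A = 0.75: 0.5 × 0.577 + 0.423 × 0.75 = 0.606

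| q | FI successes of 323 | A = 0.60 | A = 0.65 | A = 0.70 | A = 0.75 |
|---|---|---|---|---|---|
| 30% | 97 | 0.570 | 0.605 | 0.640 | 0.675 |
| 40% | 129 | 0.560 | 0.590 | 0.620 | 0.650 |
| 57.7% | 186 | 0.542 | 0.563 | 0.585 | 0.606 |
| 60% | 194 | 0.540 | 0.560 | 0.580 | 0.600 |

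**Simulation under the same null.** Each setting used 2,000 studies with 323 patients per group, a normal marker with a logistic relation to pregnancy in FI patients, and a rank test at two-sided 0.05.

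| q | A | Successful FI vs all RIF: mean AUC | Rejected | All FI vs all RIF: mean AUC | Rejected |
|---|---|---|---|---|---|
| 30% | 0.70 | 0.64 | 99% | 0.50 | 5.4% |
| 40% | 0.70 | 0.62 | 98% | 0.50 | 4.1% |
| 57.7% | 0.61 | 0.55 | 41% | 0.50 | 5.3% |
| 57.7% | 0.70 | 0.59 | 90% | 0.50 | 4.6% |
| 57.7% | 0.77 | 0.61 | 99% | 0.50 | 3.8% |

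Over all nine settings (q = 30%, 40% and 57.7%; A about 0.61 to 0.77), the stated contrast gave a mean AUC of 0.55 to 0.69 and rejected in 41% to 100% of studies. Comparing all FI with all RIF gave 0.50 and 3.8% to 5.4%.

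**The case against.** **Reading of the text.** The Study design sentence alone could be parsed with *successful* covering both groups. The Introduction and Discussion attach it to first transfers only, so the reading used here is the better one, but the wording should be settled.

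**Known successes as a reference group.** This can be a deliberate choice. Study design places the classification after transfer, and all FI patients are recruited whatever their outcome. So no data are lost, and the objection that success is unknown at the scan carries little weight. What does not survive is the interpretation as identifying RIF.

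**Stronger readings a reader might infer, which the documents do not support:**
- *A larger bias at any FI success rate.* If the marker depends only on this cycle's outcome, the contrast gives 0.3 × 0.5 + 0.7A, or 0.605 at A = 0.65 and 0.675 at A = 0.75. That is not a null of no group difference. With rates of 57.7% and 30%, all FI and all RIF already differ: 0.5 + 0.277 × (A − 0.5) = 0.542 and 0.569.
- *Confounding by age as an established error.* The number of transfers that defines RIF depends on age, and the comparison tests listed under Data statistics are unadjusted. But that paragraph is generic and separate from the SVC model, clinical data are collected, and a condensed article may leave adjustment to a fuller plan. No age gap is given.
- *Loss of the 1:1 ratio as a harm.* The ratio describes recruitment, and no stated precision or power for objective 2 depends on it.
- *A pooled pregnancy model inflated by group membership.* No section lists group as a predictor. The Abstract conflicts in wording with the sections that restrict the model to RIF; it does not fix a pooled analysis.

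**Conclusion.** The outcome selection in objective 2 stands, because it follows from the contrast that the article states. With no difference between all FI and all RIF patients, the expected AUC is about 0.56 to 0.61 at q = 57.7% and A = 0.65 to 0.75, and 0.54 to 0.675 over the wider range. The size rests on assumed values of q and A and on one common marker distribution. The spurious signal vanishes if the marker does not predict pregnancy (A = 0.5), but that would contradict the premise of objective 1. Age adjustment would not in general remove it, since the selection is on outcome. The Abstract's account of the pregnancy model is a separate and smaller inconsistency.

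**What to change.** - Define the objective 2 comparison as all 323 FI versus all 323 RIF patients on the pre-transfer scan, and report the marker–pregnancy relation within each group separately. Comparing the groups within the same outcome stratum is an alternative.
- If successful FI versus RIF is kept, label it secondary and do not interpret it as identifying RIF.
- Include age as a covariate; this is a sensible addition rather than the correction of a shown error.
- State in the Abstract which population the pregnancy model uses, in agreement with the Introduction, Study design and Sample size calculation.

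The cost is wording and analysis only, because both groups are to be recruited and scanned in any case. The reported AUC will probably be lower. All FI and all RIF may still differ because their pregnancy rates differ, so the result should be read as a group difference and not as a causal effect of RIF.
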